# 1. Introductions

Ovarian cancer is the leading cause of death for patients with gynecologic malignancies. In most cases, the disease is diagnosed at an advanced stage and approximately 75% of patients will eventually experience disease recurrence. Almost all patients with recurrent disease ultimately develop platinum resistance, which results in death. For platinum-resistant ovarian cancer, a non-platinum-based agent (i.e., liposomal doxorubicin, topotecan, gemcitabine, and etoposide) is preferred. However, the overall response rates of these single-agent therapy remain in the 10-30%. Therefore, it is important to seek alternative agent that can improve the outcomes of patients with recurrent ovarian cancer.

Apatinib is a novel orally administered small-molecule tyrosine kinase inhibitor (TKI) that selectively binds to and inhibits vascular endothelial growth factor receptor 2 (VEGFR2). A series of studies have demonstrated that apatinib exhibits encouraging antitumor activities and tolerable toxicities in several malignant tumors. In a randomized, double-blind, placebo-controlled phase III study conducted by Li et al, apatinib improved the overall survival and progression-free survival in patients with chemotherapy-refractory advanced or metastatic gastric or gastroesophageal junction adenocarcinoma. In addition, a phase 2 study by Hu et al demonstrated that apatinib had objective efficacy in heavily pretreated, metastatic non-triple-negative breast cancer with manageable toxicity.

Angiogenesis is a hallmark process in cancer and is responsible for tumor spread and metastasis. It has been shown that anti-angiogenic therapy, including anti-VEGF antibodies and VEGFR/multi-receptor TKIs, represents an attractive therapeutic strategy for ovarian cancer. Moreover, increasing evidence has suggested that the combination of anti-angiogenic therapy and single-agent chemotherapy improves the outcome of platinum-resistant ovarian cancer. Among these single drugs, oral etoposide is one of the common treatments for patients with both platinum-resistant and platinum-sensitive disease.

On the basis of prior clinical experience, we carry out this trial to explore the efficacy and safety of the combination of apatinib and oral etoposide in patients with platinum-resistant or platinum-refractory ovarian cancer.

# 2. Objectives

## 2.1 Primary Objective

• Objective response rate (ORR)

Objective response rate defined as confirmed complete response or partial response under RECIST 1.1 criteria.

## 2.2 Secondary Objectives

• Progression-free survival (PFS)

Progression-free survival is defined as the time from registration to the earlier of death or disease progression. Patients alive without disease progression are censored at the date of last disease evaluation.

• Overall survival (OS)

Overall survival is defined as the time from registration until death from any cause (or date of censoring).

• Duration of Response (DOR)

Duration of response is defined as the interval between the date of the first documented response by RECIST to the date of first disease progression or death, whichever occurred earlier.

• Disease control rate (DCR)

Disease control rate is defined as the percentage of patients who achieved a complete response, a partial response or stable disease.

• Safety data

Frequency and severity of adverse effects as defined by CTCAE version 4.03

## 2.3 Exploratory Objective

• Imaging biomarkers for predictive modeling

To evaluate whether the areas of adipose tissue measured by computed tomography (CT) could predict the efficacy of apatinib.

# 3. Study Design and Sample Size

## 3.1 Study Design

This is a phase 2, single-arm, open-label study conducted at the Sun Yat-sen University Cancer Centre.

## 3.2 Sample Size

A Simon’s two-stage design is employed with a one-sided α-error of 5% and a power of 80%. The reported data indicated that the highest objective response rate of oral etoposide monotherapy in platinum-resistant ovarian cancer was 26.7%. We expected that the objective response rate for apatinib combined with etoposide would be 50%.

Under these assumptions, eight evaluable patients will be treated in stage one and more than 2 responses are required to continue to stage two. In the second stage, 27 more patients would be enrolled for a total sample size of 35. Overall, if a total of 14 responses or more are observed, the treatment regimen would be considered a success.

# 4. Subject Population

## 4.1 Inclusion Criteria

• Histologically or pathologically confirmed diagnosis of epithelial carcinoma of the ovary.

• Platinum-resistant ovarian cancer (defined as relapsing within 6 months after the last administration of platinum-based chemotherapy) OR platinum-refractory ovarian cancer (defined as progressing while on a platinum-based chemotherapy)

• At least treated with one line of platinum-based chemotherapy

• Female, age ≥18 years and ≤70 years, signed informed consent.

• Eastern Cooperative Oncology Group (ECOG) performance status 0-2

• Measurable disease according to Response Evaluation Criteria in Solid Tumors (RECIST) 1.1 version

• Patients must have a life expectancy of at least 3 months.

• Patients must have adequate organ function as defined by the following criteria:

• White blood cell count ≥ 3 × 109/L, Absolute neutrophil count (ANC) (≥ 1.5× 109/L), Hemoglobin of ≥ 80 g/L, Platelets ≥ 70 ×109/L

• Total bilirubin ≤ 1 × upper limit of normal (ULN), AST and ALT ≤ 2 × ULN

• Serum creatinine ≤ 1 × ULN

## 4.2 Exclusion Criteria

• Had prior exposure to apatinib or has known allergies to any of the excipients.

• History of myocardial infarction, or unstable angina, or New York Heart Association (NYHA) Grade III-IV within 6 months prior to Day 1.

• Patients with QT interval prolongation

• Serious, non-healing wound, active ulcer, bowel obstruction

• History of abdominal fistula or gastrointestinal perforation within 28 days prior to Day 1

• Evidence of bleeding diathesis or coagulopathy

• Inadequately controlled hypertension

• Major surgical procedure within 28 days prior to Day 1

• Symptomatic central nervous system (CNS) metastasis

# 5. Treatment and Administration

• Apatinib combined with oral etoposide

• Apatinib, 500 mg, administered orally once daily

• Oral etoposide, 50 mg, administered on days 1 to 14. The administration of oral etoposide will be repeated every 3 weeks for a maximum of six cycles

Treatment was continued until disease progression, patient withdrawal, or unacceptable toxic effects.

# 6. Dose Modification

## 6.1 Dose Interruptions

Dose interruptions are required on the occurrence of grade 3 or worse toxicities. Treatment has to be delayed until recovery to ≤ grade 2 hematological or ≤ grade 1 nonhematological toxicities. Repeat dose interruptions are allowed for a maximum of 14 days on each occasion.

## 6.2 Dose Reductions

Dose reductions will be made on the basis of the worst drug-related toxicity. However, investigators may also reduce the dose of either or both study drugs for toxicity, as clinically warranted. Table 1 shows the dose levels that will be used when dose reductions are required. Patients who experience toxicity meeting the criteria cited in Table 2 will have a dose level reduction as specified in Table 1.

**Table 1. Dose level reductions —— Apatinib + Oral etoposide**

| Dose Level | Apatinib | Oral etoposide |
| --- | --- | --- |
| Starting level | 500mg/d，qd | 50mg/d，d1-d14 |
| Level-1 | 500 mg & 250 mg taken respectively every other day | 50mg/d，d1-d12 |
| Level-2 | 250mg/d，qd | 50mg/d，d1-d10 |

**Table 2. Dose reductions for toxicity**

| Toxicity | Worst CTC grade | | | Apatinib | Oral etoposide | |
| --- | --- | --- | --- | --- | --- | --- |
| Hematologic | | 1-2 | Not reduction | | | Not reduction |
| 3-4 | First occurrence: Not reduction | | | Decrease 1 level |
| Any occurrence after first occurrence: Decrease 1 level | | |
| Nonhematologic | |  |  | | |  |
| Hypertension,  Proteinuria，  Hand-foot syndrome | | 1-2 | Not reduction | | | Not reduction |
| 3 | First occurrence: Not reduction | | | Not reduction |
| Any occurrence after first occurrence: Decrease 1 level | | |
| 4 | Decrease 1 level | | | Not reduction |
| Others* | | 1-2 | Not reduction | | | Not reduction |
| 3 | First occurrence: Not reduction | | | Decrease 1 level |
| Any occurrence after first occurrence: Decrease 1 level | | |
| 4 | Decrease 1 level | | | Decrease 1 level |

*Other nonhematologic toxicities, e.g., elevated ALT/AST, elevated bilirubin, nausea, vomiting, and anorexia.

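### No rule requires apatinib to stop after a drug-related gastrointestinal perforation, fistula, myocardial infarction or unstable angina; Table 2's open Others row sets a restart dose instead

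*Protocol*

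**What the plan says.** Section 5 gives the end of treatment: "Treatment was continued until disease progression, patient withdrawal, or unacceptable toxic effects". The toxicity limb is not defined there or anywhere else in the protocol.

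Section 6.1 requires an interruption for any toxicity of grade 3 or worse. On restarting it says: "Treatment has to be delayed until recovery to ≤ grade 2 hematological or ≤ grade 1 nonhematological toxicities". On duration it says: "Repeat dose interruptions are allowed for a maximum of 14 days on each occasion". It gives no minimum wait and does not say what follows if recovery takes longer than the maximum.

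Section 6.2 states: "Dose reductions will be made on the basis of the worst drug-related toxicity". It directs that patients who meet the Table 2 criteria are reduced as Table 1 sets out, and adds: "However, investigators may also reduce the dose of either or both study drugs for toxicity, as clinically warranted".

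Table 2 gives separate non-haematological rules only for hypertension, proteinuria and hand-foot syndrome. The rest fall under Others, with the footnote "Other nonhematologic toxicities, e.g., elevated ALT/AST, elevated bilirubin, nausea, vomiting, and anorexia". In that row:
- First grade 3 event: apatinib is not reduced; etoposide goes down one level.
- Later grade 3 events: apatinib goes down one level.
- Grade 4: both drugs go down one level.

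In Table 1, the first apatinib reduction is "500 mg & 250 mg taken respectively every other day".

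Section 4.2 excludes from entry patients with abdominal fistula or gastrointestinal perforation in the previous 28 days, and patients with myocardial infarction or unstable angina in the previous 6 months.

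**The concern.** The footnote's examples are laboratory and tolerability events, for which holding the drug and resuming it is reasonable. Because the list is open and nothing is carved out, the same rule also governs perforation, fistula, infarction and unstable angina when they are judged drug-related. For these the protocol writes down a dose to resume at, and leaves stopping to a term that it does not define.

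The protocol has already judged recent events of these kinds too risky for a first dose. An event on treatment that has been attributed to the study drug is hardly a lesser warning, yet the on-treatment rules carry no trace of that judgement. Two patients with the same event could be handled differently, one re-exposed and one stopped, without either being a protocol deviation. What is at stake is patient safety.

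**Working it through.** The protocol gives no figure of its own on this point, so the check follows a patient through the rules and then compares the time limits.

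**1. Which row applies.** Perforation, fistula, infarction and unstable angina are not haematological and are not among the three separately named toxicities. Only Others remains.

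**2. Dose at restart**, for a patient on the starting level (Tables 1 and 2):
- First grade 3 event: no reduction, so 500 mg/d, which is 500/500 = 100%.
- Grade 4 event: Level-1, alternating 500 mg and 250 mg. Mean (500 + 250)/2 = 375 mg/d, which is 375/500 = 75%.

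**3. Earliest restart.** Section 6.1 asks only for recovery to grade 1 or less. No minimum number of days is set.

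**4. Is there a mandatory stop elsewhere?**
- Section 5 ends treatment for unacceptable toxicity, but ties the term to no event or grade.
- Section 6.2 gives discretion to reduce the dose, not a duty to stop.
- Section 9.2 requires serious events to be reported to the IRB within 24 hours; it does not require a stop.
- Sections 9.4 and 10.2.3 record and summarise discontinuations; they do not trigger them.

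None of these requires a stop for the four named events.

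**5. Comparison with section 4.2, under a condition.** Assume that the 14-day maximum also covers a first interruption, and that the interruption starts at onset. Take 6 months as 182 days (range 181 to 184). The latest permitted restart is then day 14:
- Perforation or fistula: 28 − 14 = at least 14 days still inside the entry window.
- Infarction or unstable angina: 182 − 14 = about 168 days still inside it (range 167 to 170).

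If the maximum covers only second and later interruptions, there is no latest restart day after a first event and these two differences do not follow. Steps 1 to 4 do not use the maximum and stand on either reading.

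**The case against.** The best case for the protocol has several parts.

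- **Section 5 already ends treatment for unacceptable toxicity.** It stands beside progression as an end of treatment and is more than an option. Investigators bound by GCP would very probably apply it to a perforation or an infarction. This stands. What remains is that the term is undefined, while Table 2 supplies a definite dose for the same event.
- **Table 2 sets dose levels and does not authorise a restart.** This also stands. A reader might infer that the protocol orders re-exposure at full dose. It does not; it permits it.
- **Entry and restart criteria serve different purposes.** The protocol separates them elsewhere: entry requires bilirubin no higher than the upper limit of normal, while restart after a toxicity is framed as grade 1 or less. A reader might infer that 6.1 contradicts 4.2. Section 4.2 governs entry only and, for these events, implies a waiting period, so the two are not in formal conflict.
- **The 14-day limit is worded for repeat interruptions.** A reader might infer that every permitted restart falls inside the 4.2 windows. That needs the limit to cover first interruptions too, which the text leaves unclear.
- **The conditions narrow the case.** The event must be judged drug-related, recover to grade 1 or less, and not be judged unacceptable. That is less plausible after perforation, fistula or infarction than after treated angina.

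A reader might also put QT prolongation on the same footing, since 4.2 excludes "Patients with QT interval prolongation". That is weaker. The criterion has no look-back period, so once the interval has normalised it no longer clearly bars a first dose, and sections 7.1 and 7.2 schedule an ECG at screening only.

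**Conclusion.** The concern holds in a limited form. For drug-related perforation, fistula, infarction and unstable angina, the only specific written response is to resume apatinib at 100% of the starting dose after a first grade 3 event, or 75% after grade 4, once the event has recovered to grade 1 or less. No rule requires a stop. This is an inconsistent safety standard between entry and treatment.

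The dose figures assume a patient on the starting level and an event attributed to the drug. The day counts of 14 and about 168 hold only if the 14-day maximum applies to a first interruption. Event frequency is not given, so no expected number of patients can be stated; the planned maximum is 35.

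The point does not touch the Simon design, its error rates or the ORR definition. It deserves an amendment because the events can be fatal and the remedy is small.

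**What to change.** Add a line to Table 2 that overrides the Others row, and a matching sentence to section 5: drug-related gastrointestinal perforation, fistula, myocardial infarction or unstable angina count as unacceptable toxicity and permanently end apatinib. Leave all other toxicities under the existing rows.

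Two wider changes are not needed for this point. Ending treatment whenever recovery exceeds 14 days would reach every toxicity of grade 3 or worse, including haematological toxicity, and is a separate trade-off. A dose rule for grade 3 QT prolongation would depend on ECGs that the treatment phase does not schedule.

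The cost is a protocol amendment of one table line and one sentence, with no extra patients or procedures. A permanent stop is stricter than the waiting period that 4.2 implies, so an occasional patient would leave apatinib earlier. With 35 patients in the denominator, each such patient who is not yet a confirmed responder lowers the ORR by at most 1/35 = 2.9 percentage points.

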# 7. Study Procedures

## 7.1 Screening Phase

Screening procedures to be completed within 30 days before treatment:

• Signed informed consent

• Review of eligibility criteria

• Review of medical history and demographics

• Physical examination

• Vital signs

• Eastern Cooperative Oncology Group (ECOG) performance status

• Laboratory tests including hematology and serum chemistry, and urine routine.

• Tumor markers, including CA125, CA199, and HE4.

• ECG

• Tumor assessments, including radiographic imaging of the chest, abdomen and pelvis by computed tomography (CT) or magnetic resonance imaging (MRI).

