## 7.2 Treatment Phase

During the treatment of oral etoposide combined with apatinib, patients had to come to outpatient clinic every 3 weeks. When six cycles of oral etoposide in combination with apatinib were completed, apatinib monotherapy was continued and patients had to come to outpatient clinic every one month.

• Laboratory tests including hematology and serum chemistry, and urine routine. Urinary protein quantity in 24 hours will be tested if urinary protein is 2+

• Tumor markers, including CA125, CA199, and HE4.

• Tumor assessment. Tumor response according to RECIST version 1.1 is assessed using computed tomography (CT) or magnetic resonance imaging (MRI) after two, four, and six cycles of oral etoposide, and subsequently every 2 months during apatinib monotherapy until confirmed disease progression.

In case of clinical progression, the date of progression will be defined as the date of the first imaging study that documents progression.

• Adverse events will be reported by the patients and be followed by the investigator until resolution or until a clinically stable endpoint is reached.

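### Screening urine protein is neither quantified nor tied to an entry criterion, so a patient with proteinuria of grade 3 or worse and creatinine within normal limits may start full-dose apatinib

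*Protocol*

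**What the plan says.** Section 7.1 lists the tests to be done within 30 days before treatment, among them "Laboratory tests including hematology and serum chemistry, and urine routine". It sets no threshold for the urine result and no follow-up of a positive one.

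Section 4.1 introduces its laboratory limits with "Patients must have adequate organ function as defined by the following criteria". The only renal item in that list is "Serum creatinine ≤ 1 × ULN". Section 4.2 names neither proteinuria nor renal disease.

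Section 5 starts every patient at the same dose: "Apatinib, 500 mg, administered orally once daily".

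Quantification appears under 7.2, Treatment Phase: "Urinary protein quantity in 24 hours will be tested if urinary protein is 2" (the printed threshold is 2+). In that phase, while etoposide is given, "patients had to come to outpatient clinic every 3 weeks".

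On study, 6.1 states that "Dose interruptions are required on the occurrence of grade 3 or worse toxicities", and non-hematological toxicity must be back to grade 1 or lower before dosing resumes. Section 6.2 adds that "Patients who experience toxicity meeting the criteria cited in Table 2 will have a dose level reduction as specified in Table 1". Table 2 groups proteinuria with hypertension and hand-foot syndrome. In that group apatinib is lowered for a repeated grade 3 or for grade 4, and etoposide is left unchanged.

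**The concern.** The protocol treats proteinuria as a toxicity of apatinib: it has its own line in the dose-reduction table, and a 2+ reading during treatment calls for a 24-hour collection. The same reading before the first dose has no written consequence. The test is already done at screening, but its result decides nothing.

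What is at stake is the safety of the individual patient. Someone with heavy proteinuria can meet every written criterion and start a VEGFR2 inhibitor at full dose, at a level that would stop dosing had it arisen on study.

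There is a lesser consequence for the safety data. Section 9.1 counts as adverse events those that are new or have worsened from baseline. Without a 24-hour value at baseline, worsening of existing proteinuria has to be judged against the screening urine routine alone.

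**Working it through.** The protocol gives no figure to reproduce, so the check sets its sections side by side.

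**1. Does any entry criterion use urine protein?**
- Laboratory limits in 4.1: white cells, neutrophils, hemoglobin, platelets, total bilirubin, AST, ALT, creatinine. That is 8, of which 0 concern urine protein.
- Exclusions in 4.2: prior apatinib or allergy; cardiac history; QT prolongation; wound, ulcer or bowel obstruction; fistula or perforation; bleeding or coagulopathy; hypertension; major surgery; CNS metastasis. That is 9, of which 0 concern urine protein.
- Section 4.1 says that adequate organ function is defined by its list, so the list reads as closed. Neither section has a clause leaving other conditions to the investigator's judgement.

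**2. Is a 2+ result quantified before the first dose?** Section 7.1 does not ask for it. The instruction stands only under 7.2.

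**3. How are the other toxicities of Table 2 handled at entry?** The comparison covers those measured by a laboratory test or a vital sign.

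| Toxicity named in Table 2 | Entry limit |
| --- | --- |
| Hematologic | Yes: blood-count limits (4.1) |
| ALT/AST | Yes: at most 2 × ULN (4.1) |
| Bilirubin | Yes: at most 1 × ULN (4.1) |
| Hypertension | Yes: excluded if inadequately controlled (4.2) |
| Proteinuria | None |

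Proteinuria is the only one of the five without an entry limit.

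**4. How does entry compare with the rules on study?**

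| Proteinuria | Before the first dose | On study (6.1) |
| --- | --- | --- |
| Grade 3 or worse | Eligible if creatinine is at or below 1 × ULN and all else is met | Dosing held |
| Grade 2 | Eligible on the same terms | After a hold, dosing may not yet resume |
| Grade 1 or lower | Eligible | Dosing may resume |

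Entry is thus looser than both the hold rule and the resumption rule.

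**5. What cannot be worked out.** The protocol grades by CTCAE 4.03 but does not print the proteinuria cut-offs, so a 2+ reading cannot be assigned a grade from the document. It also gives no prevalence of proteinuria at baseline, so the number of patients affected cannot be estimated.

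**The case against.** **Entry rules and toxicity rules serve different purposes.** This is true, and no sentence in the sections cited contradicts another. A line in Table 2 does not by itself imply an entry limit: hand-foot syndrome shares the line with proteinuria and has none, and neither do nausea, vomiting and anorexia. The point therefore rests on the narrower comparison with toxicities measured by laboratory test or vital sign, and on the fact that the screening urine test is already done.

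**There are partial safeguards.** The creatinine limit, the hypertension exclusion and conduct under GCP all reduce the concern, and an investigator could decline such a patient. None of these is a written limit on urine protein, so the gap is narrowed but stays open.

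**Stronger readings are not supported.**
- A reader might infer that proteinuria would go unseen until treatment had begun. It would not: the screening urine routine shows it before the first dose. What is missing is the 24-hour value and a cut-off.
- A reader might infer that a 2+ is never quantified in this trial. Section 7.2 requires it during treatment.
- A reader might count doses taken before the first visit at week 3. Section 7.2 does not say whether urine is tested on day 1, so the count could be 0 to 21 (3 × 7), and it would not measure harm.
- A reader might infer that unchanged baseline proteinuria must trigger the hold in 6.1. Section 9.1 speaks of new or worsened events, so the protocol leaves that open.

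**Conclusion.** The point holds as a gap in eligibility and screening. A patient whose screening urine shows heavy protein, with creatinine at or below 1 × ULN, may start apatinib 500 mg daily without quantification, even at grade 3 or worse.

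In terms of the text, its size is 0 of 8 laboratory limits, 0 of 9 exclusions, and one of five laboratory or vital-sign toxicities in Table 2 left without an entry limit. The conclusion assumes that the lists in 4.1 and 4.2 are applied as written, and that the screening urine routine reports protein, as 7.2 implies for the same test.

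It is a minor safety improvement, not a flaw in the statistical design. The objective response rate, the two-stage rule and the sample size of 35 are unaffected. Eligibility criteria belong in the protocol, so a separate statistical analysis plan would not be expected to settle it.

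**What to change.** 1. **Section 7.1:** extend the existing treatment-phase rule to screening. If urine protein is 2+ or higher, measure 24-hour urine protein, have the result before the first dose, and record it as the baseline.
2. **Section 4.2:** exclude at least proteinuria of grade 3 or worse by CTCAE 4.03, the version already in use. This matches the hold level in 6.1 but not its resumption level, since a patient at grade 2 could still start. The sponsor may prefer to exclude grade 2 or worse, which would match the requirement in 6.1 for recovery to grade 1 or lower.

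The cost is two lines of text and a 24-hour collection for patients at 2+ or higher only. The trial already uses this non-invasive test, and it fits within the 30-day screening window. There may be a few screen failures, more if the grade 2 limit is chosen.
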